### Intervention

All research activities will take place at the PERFORM Centre, Concordia University. This center houses 8000m^2^ of laboratories, assessment suites, and lifestyle intervention spaces. It is equipped with the instruments needed to assess this study’s primary outcomes (MRI, Ultrasound), as well as space for conducting the intervention.

All participants will receive treatment with the StimaWELL 120MTRS system (schwa-medico, Germany) (Fig. 2). The StimaWELL 120MTRS system is a pre-modulated IFC (interferential current) electrotherapy device. It delivers current across up to 12 channels and offers preset pain and muscle therapy programs. The device also heats up to 40 °C.

**Fig. 2 Fig2:**
[figure not shown]
StimaWELL 120MTRS system

#### Phasic intervention group

Participants in this group will receive therapy at the StimaWELL 120MTRS system’s setting for phasic muscle stimulation of the lumbar spine (3 kHz, modulation 50 Hz). Tonic muscles are postural muscles composed of a majority of type I fibers, while phasic muscle are prime movers composed of a majority of type II fibers. We are choosing the phasic setting because some research has shown an increase in stiffness in the superficial multifidus (SM) in CLBP patients9, which contain a greater proportion of type II fibers in healthy individuals. The increase in stiffness could reflect a shift towards type I fiber composition in the SM in CLBP patients. Therefore, parameters which selectively target type II fibers might help reverse this process. During the initial calibration and throughout the treatments, the current intensity will be increased so that participants feel a strong but comfortable contraction. This standard of current intensity will always be maintained, although the actual output may vary over the course of treatment.

#### Combined (tonic and phasic) group

Participants in this group will receive therapy at the StimaWELL 120MTRS system’s setting for combined stimulation (3 kHz, modulation 4 Hz and 50 Hz). We are investigating the efficacy of the combined setting since 23–46% of multifidus fibers are type II fibers[31]. A treatment that targets these fibers should also leads to improvements in multifidus physiology. During the initial calibration and throughout the treatments, the current intensity will be increased until participants feel a strong but comfortable contraction. This standard of current intensity will always be maintained, although the actual output may vary over the course of treatment.

#### Timeline

The intervention period will last 10 weeks, with treatments occurring twice a week for both groups. There is evidence that a minimum of five weeks of training are needed to induce muscular hypertrophy[32]. The treatment will last 20 min for the first 3 weeks, 25 min for the second 3 weeks, and 30 min for the last 4 weeks; these times are in line with norms for NMES interventions[25]. Additionally, participants will come to the PERFORM Centre for two pre-intervention visits (trial visit & questionnaire completion, MRI and ultrasound evaluation), and one post-intervention visit (questionnaire completion, MRI and ultrasound evaluation) for a total of 23 visits (Table 1).

**Table 1 Tab1:** Schedule of enrolment, interventions, and assessments

	Enrolment	Baseline	Intervention			Post-Intervention
TIMEPOINT	*-t*_*1*_	0	*t*_*1 – 10*_	*t*_*11*_	*t*_*12-20*_	*t*_*21*_
ENROLMENT:						
Eligibility screen	X					
Informed consent		X				
Neurological screen		X				
Trial of wave-mat		X				
Allocation		X				
INTERVENTIONS:						
Phasic Group			X	X	X	
Combined Group			X	X	X	
ASSESSMENTS:						
NPRS Full		X		X		X
NPRS Pre-Post			X		X	
ODI	X	X		X		X
BPI		X		X		X
PCS		X		X		X
MRI		X				X
Ultrasound		X				X

-**t**_1_ = pre-intervention; 0 = baseline visit; ***t***_***1****** – ******10***_ = treatments 1–10; ***t***_***11***_ = treatment 11; ***t***_***12-20***_ = treatments 11–20; ***t***_***21***_ = post-intervention visit

### Primary outcome measures

#### MRI assessment of multifidus morphology

All participants will undergo a lumbosacral MRI evaluation using the PERFORM Centre’s 3-T GE machine to assess multifidus muscle CSA and fat infiltration. MR imaging will be collected using a standard phased-array body coil with 4-mm slice thickness, 180-mm2 field of view and 512 × 512 matrix. Quantitative multifidus muscle measurements will be obtained from axial T2-weighted images, bilaterally at the L4-L5 and L5-S1 spinal levels, which are the most relevant levels for spinal pathologies. The multifidus muscle CSA will be measured manually at both levels on multiple slices to calculate the summative 3D volume; cross-sectional area measurements have been widely used to assess muscle size and this technique is very reliable (ICCs:0.97–0.99)[33]. Multifidus muscle composition (e.g., fatty infiltration) will be assessed using IDEAL (Lava-flex, 2 echo sequence) fat and water images by calculating percent-fat signal fraction at each spinal level according to the following equation: %FSF = (Signal_fat_/[Signal_water_ + Signal_Fat_] × 100)[34].

#### Ultrasound assessment of multifidus muscle function

The PERFORM Centre’s Aixplorer ultrasound unit (Supersonic Imagine, Aix-en-Provence, France) will be used to assess multifidus muscle contraction and stiffness. First, participants will be placed in a prone position, on a therapy table, with a pillow placed under their abdomen to minimize lumbar lordosis (e.g., maximum of 10° measured with an inclinometer) and instructed to relax the paraspinal musculature. The spinous process of L5 will be palpated and marked on the skin with a pen prior to imaging. Acoustic coupling gel will be applied to the skin and the ultrasound transducer placed longitudinally along the midline of the lumbar spine to confirm the location of the L5 level. The multifidus muscle will be imaged bilaterally, in the parasagittal section, allowing for the visualization of the L5/S1 zygapophyseal joints. Multifidus muscle contraction, expressed as the % thickness change from a rested to contracted position, will be assessed via contralateral arm lifts while holding a small handheld weight (e.g., 1.5 to 3 pounds) based on the participant’s body weight. Participants will be instructed to raise the loaded arm 5 cm off the examination table with the shoulder in 120° of abduction and elbow 90° of flexion, following a deep inhalation and exhalation. Images will be taken after the loaded arm has been held for 5 s. The handed weight is designed to load the multifidus muscle to approximately 30% of maximal voluntary isometric contraction. Measurements will be obtained at L4-L5 and L5-S1 and repeated 3 times, both at rest and during contraction on each side. The average of 3 thickness ratios ([thickness contracted – thickness rest / thickness rest] × 100) will be calculated in used in the analysis. This technique is valid and reliable[35, 36].

The same position and procedure will be used to assess multifidus muscle stiffness with shear-wave elastography. This technique is based on a compressive wave that propagates within the tissue, allowing for the calculation of tissue shear wave modulus while rendering a quantitative color-coded map of tissue elasticity. Participants will be lying prone on the therapy table for 5 min before the lumbar multifidus is imaged at rest and during sub-maximal contractions while performing the same task as described above. Three repetitions will be performed on each side (both at L4-L5 and L5-S1) and the average shear wave modulus will be used for analysis. Finally, multifidus muscle stiffness will also be examined in a standing position when the muscle is naturally contracting in a stabilizing role. Participants will be asked to stand barefoot on the floor with their arms relaxed on each side. To achieve a habitual standing posture, they will be instructed to march on a spot for a few seconds and remain on the position where their feet landed. Resting shear wave modulus measurements will be acquired as described above and obtained in the standing fundamental position (e.g., arms resting naturally on each side of the body). Again, three measurements will be obtained on each side (both at L4-L5 and L5-S1) and the average shear wave modulus will be used in the analysis. This technique is valid and reliable[37–39].

### Secondary outcome measures

#### Pain intensity

Pain intensity will be measured with the Numerical Pain Rating Scale (NPRS). The NPRS measures pain intensity on a scale of 0—10, with 0 indicated no pain, and 10 indicating the worst pain imaginable. Changes of 2 or more points are clinically significant[40]. At baseline, midpoint, and endpoint, participants will be asked to rate the following using the NPRS: current low back pain, current leg pain, best and worst pain low back pain over the previous week, pain sitting and with movement over the past 24 h. Additionally, participants will be asked to rate their current low back pain prior to, and at the end of each treatment.

#### Pain interference

Pain interference will be measured using the Brief Pain Inventory, interference subsection (BPI). The BPI-I is a 7-item questionnaire that measures how pain interferes with activities of daily living. Each item is rated from 0–10. Higher scores indicate greater interference.

#### Disability

Disability will be assessed using the Oswestry Disability Index (ODI, is used to measure disability in relation to LBP. It is a 10-item scale in which each item is rated from 0–5. Higher scores indicate greater disability, and changes of > 10% are clinically significant[27].

All three questionnaires are valid and reliable measures of LBP and function[27, 40, 41].

### Possible effect modifiers

#### Catastrophizing

Pain catastrophizing will be assess using the Pain Catastrophizing Scale (PCS). The PCS is a 13-item questionnaire that assesses the participant's level of catastrophizing. Each item is rated from 0–4 for a possible total of 52. Higher scores indicate greater catastrophizing, with scores above 30 being clinically significant[42].

Participants will complete the BPI, ODI, and PCS at baseline, midpoint (6-weeks), and post-intervention (11-weeks).

### Procedure

#### Trial visit

Participants who pass the phone screening will be invited for a trial visit. Upon arrival, the PhD student will ask them to sign a consent form. Second, the PhD student will assess lumbosacral dermatomes and myotomes to ensure the absence of nerve root compression. Third, participants will fill out a sociodemographic questionnaire, as well as questionnaires regarding secondary outcomes (see above). Fourth, participants will receive a 10-min trial treatment with the StimaWELL 120MTRS system at its setting for ‘combined’ lumbar muscle therapy.

#### Wave-mat calibration

The StimaWELL 120MTRS system delivers current at a given intensity across up to 12 channels. However, in the presence of pain or injury the current may not be felt equally across channels. Therefore, prior to the trial, the wave-mat will be calibrated to ensure that the current is equally felt across all channels. A paper towel will be sprayed with warm water and laid over top of the wave-mat. Participants will be asked to remove their top (and unbuckle their bra, if applicable), lie supine on the towel with knees bent, and lower the top of their underwear so that their coccyx is touching the lowest channel. A blanket will be provided for privacy. During the initial phase of calibration, the current travels the length of the wave-mat, from bottom to top, in repetitive fashion. The current will be increased to tolerance (e.g., until participants feel a strong, but non-painful, sensation). Then, the current will be adjusted, channel by channel (from bottom to top), to ensure that each channel is set to the appropriate intensity. Once this is complete, the current will be adjusted from side-to-side, in groups of two channels (from bottom to top), to ensure the intensity is the same from one side to another at a given level. This completes the calibration. This process will be repeated prior to the start of participants’ 5^th^, 9^th^, 13^th^, and 17^th^ treatments, to account for unilateral and segmental adaptations, and to ensure the multifidus is appropriately stimulated.

### Data monitoring

#### Adverse events

The occurrence of adverse events in response to the treatment (ex: muscle soreness, temporary increase in pain or stiffness) will be monitored by the PhD student during the intervention using open-ended questions.

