#### Co-interventions

Participants will be asked about co-interventions (physiotherapy visits, medication, exercise, injection) during each visit. Any co-interventions will be recorded.

Treatment modification3.

During all sessions, participants will be provided a remote to increase or decrease the intensity of the current to tolerance, as needed.

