### Sample size calculation

While the effect of NMES on multifidus muscle morphology and function has not been thoroughly investigated in subjects with CLBP, previous reports showed significant improvements in multifidus thickness at rest and during contraction with medium to large effect sizes following a 6-week[19] and single NMES session[43], respectively. Based on these studies, we used a mean effect size of 0.9 to calculate our sample size at a level of confidence of 0.05 and 80% power. Accordingly, a sample size of 12 participants in each group was needed. We increased the sample size to 15 participants in each group to account for potential drop-out.

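### As worded, adverse-event monitoring stops before the post-intervention visit and covers only events attributed to treatment, so event counts may be somewhat understated (minor)

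*Protocol article*

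**What the plan says.** The Adverse events section is one sentence that fixes scope, window, assessor and method. The scope is "The occurrence of adverse events in response to the treatment", with soreness and short-lived rises in pain or stiffness as examples. These "will be monitored by the PhD student during the intervention using open-ended questions". The Personnel section says that this student is not blinded to allocation and also administers the intervention.

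The Timeline section defines the period: "The intervention period will last 10 weeks, with treatments occurring twice a week for both groups". It lists two pre-intervention visits and one post-intervention visit separately, and gives questionnaires, MRI and ultrasound as the content of the last. Table 1 makes the same split between intervention and post-intervention columns.

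Under Trial visit, before the intervention period starts, "participants will receive a 10-min trial treatment with the StimaWELL 120MTRS system at its setting for ‘combined’ lumbar muscle therapy".

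The Co-interventions section, which comes next, uses a wider window: "Participants will be asked about co-interventions (physiotherapy visits, medication, exercise, injection) during each visit".

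**The concern.** The reactions that the protocol gives as examples can appear hours or days after a session, so they are often found at the next contact. For treatments 1 to 19 the next contact is another treatment. For treatment 20 it is the post-intervention visit, which the stated window does not include.

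The second limit is the scope. If only events in response to the treatment are monitored, someone must judge the cause before an event qualifies. Here that person knows the allocation and delivers the stimulation. An event not linked to treatment at the time need not be written down, and no later analysis can recover it.

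What is at stake is the completeness of the safety record. The Background says that tolerance matters for how much current a patient can take, and reports a claim that medium-frequency current is more comfortable. Readers will therefore look at the harm data, even though no tolerability endpoint is defined.

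**Working it through.** **Visits.** The Timeline gives 10 weeks × 2 treatments = 20 treatments. Adding 2 pre-intervention visits and 1 post-intervention visit gives 2 + 20 + 1 = 23, which agrees with the protocol's stated total. The co-intervention question applies at all 23. Read literally, the adverse-event window applies at the 20 treatment visits.

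**Exposures.** One trial session plus 20 treatments gives 21 stimulation exposures per completer.

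**First later question inside the stated window:**

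| Exposure | Next visit inside the window |
|---|---|
| Trial session | Treatment 1, for those who continue |
| Treatments 1 to 19 | The following treatment |
| Treatment 20 | None stated (t21 is post-intervention) |

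So one exposure of 21 has no later question: 1/21 = 4.8%. A reaction felt during treatment 20 itself is still inside the window; only a delayed one is lost.

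**Duration.** The Timeline states: "The treatment will last 20 min for the first 3 weeks, 25 min for the second 3 weeks, and 30 min for the last 4" (the final figure is again in weeks). Treatment time is 6 × 20 + 6 × 25 + 8 × 30 = 120 + 150 + 240 = 510 min, and 520 min with the 10-min trial session. Treatment 20 contributes 30/520 = 5.8%.

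**Effect on incidence (illustration only).** The document gives no adverse-event rate. Assume a constant, independent risk p of a delayed reaction per exposure, a participant who completes all sessions, every reaction to the first 20 exposures elicited, and every delayed reaction to the last one missed. The proportion with at least one reaction is 1 − (1 − p)^k, with k = 20 seen and k = 21 true:

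| Assumed p | Seen (k = 20) | True (k = 21) | Shortfall (points) |
|---|---|---|---|
| 0.01 | 18.2% | 19.0% | 0.8 |
| 0.05 | 64.2% | 65.9% | 1.8 |
| 0.10 | 87.8% | 89.1% | 1.2 |
| 0.20 | 98.8% | 99.1% | 0.2 |

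The shortfall equals p(1 − p)^20. It is largest at p = 1/21, where it is (1/21)(20/21)^20 = 0.018. Under this model the window alone costs at most about 1.8 percentage points.

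**Attribution filter.** No arithmetic is possible, because the document gives no rate of events and no rate of attribution. The reasoning is textual: the scope phrase restricts what is monitored, and the person applying it is the unblinded treatment provider.

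**Cover from other measures.** Under Pain intensity, current low back pain is rated before and at the end of each treatment. At the endpoint visit, participants also rate current back and leg pain, best and worst back pain over the past week, and pain sitting and moving over 24 h. This would pick up part of a pain flare after treatment 20. It does not ask about soreness or stiffness, and a pain score is not an event record. At the trial visit the questionnaires come before the stimulation, so the baseline rating cannot reflect a reaction to it.

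**The case against.** The strongest reply is that this is one summary sentence in a condensed article. It does not say that events are asked about at no other time, and a fuller protocol may describe forms, relatedness grading and follow-up. Open-ended questions filter little, and no attribution procedure is described. Table 1 has no adverse-event row, but it has no co-intervention row either, so nothing follows from that.

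Much of this stands, and it is why the point is minor. It does not remove the point. The sentence states a scope and a window, and a fuller document would have to widen both rather than merely add detail. The neighbouring section shows that the authors wrote a question for each visit where they intended one.

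Three stronger readings are tempting and not supported:

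- *A reader might infer that a tolerability comparison between arms is biased low.* The Statistical analysis section plans no such comparison. Under-counting in both arms gives a difference no known direction, and the trial session uses the same setting for everyone.
- *A reader might infer that events behind drop-out are lost.* The document is silent on contact after stopping, and someone who stops early is still within the 10-week period. The Sample size calculation says "We increased the sample size to 15 participants in each group to account for potential drop-out". This is an allowance, not an expected rate, and it does not link drop-out to reactions.
- *A reader might count two exposures, the trial session and the last, as having no later question.* Treatment 1 is inside the window and can elicit a reaction to the trial session from anyone who continues, so only the last exposure qualifies.

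**Conclusion.** The point holds as a minor one. Read with the Timeline, the stated window leaves delayed reactions to treatment 20 without a stated adverse-event question: 1 of 21 exposures (4.8%), in the longest-session block and only partly covered by the endpoint pain ratings. The trial session is covered late, from treatment 1, and only in those who go on. The scope limit is the more important half, because an event not attributed to treatment at the time need not be recorded. Its size cannot be given.

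The conclusion is that adverse-event counts may be understated. It rests on a literal reading of the window and scope, and on the intervention meaning the 10-week treatment period. The primary outcomes, sample size and planned analyses are unaffected.

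**What to change.** Make two wording changes in the Adverse events section:

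1. Align the window with the co-intervention rule: ask at each visit from the trial treatment through the post-intervention visit (t21).
2. Record all adverse events whatever the cause, with relatedness to treatment as a separate field.

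The cost is one question at visits that already take place and one extra field on the form. The downside is a slightly higher event count that includes unrelated events; the relatedness field lets these be reported separately.

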#### Co-interventions

Participants will be asked about co-interventions (physiotherapy visits, medication, exercise, injection) during each visit. Any co-interventions will be recorded.

Treatment modification3.

During all sessions, participants will be provided a remote to increase or decrease the intensity of the current to tolerance, as needed.

### Sample size calculation

While the effect of NMES on multifidus muscle morphology and function has not been thoroughly investigated in subjects with CLBP, previous reports showed significant improvements in multifidus thickness at rest and during contraction with medium to large effect sizes following a 6-week[19] and single NMES session[43], respectively. Based on these studies, we used a mean effect size of 0.9 to calculate our sample size at a level of confidence of 0.05 and 80% power. Accordingly, a sample size of 12 participants in each group was needed. We increased the sample size to 15 participants in each group to account for potential drop-out.

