## Abstract

**Background:**

Neuromuscular electrical stimulation (NMES) is used to improve muscle strength clinically when rehabilitating various musculoskeletal disorders. However, the effects of NMES on muscle morphology and function in individuals with non-specific chronic low back pain (CLBP) have scarcely been investigated. Although research links deficits in the paraspinal musculature with subjective reports of pain and disability, it is unknown if treatment with NMES can help reverse these deficits. Therefore, the primary aim of this study is to compare the effects of two muscle therapy protocols with a medium-frequency electrotherapy device (the StimaWELL 120MTRS system) on multifidus muscle morphology and function in CLBP patients. The secondary aims are to determine the effects of these protocols subjective reports of pain intensity, pain interference, disability, and catastrophizing.

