Electrical stimulation therapy is a treatment modality commonly used to treat pain and muscle dysfunction. Specifically, clinicians use neuromuscular electrical stimulation (NMES) to restore strength and muscle function following atrophy or loss of neuromuscular control. NMES preferentially stimulates alpha motor neurons, causing involuntary muscular contraction. Over time, the treatment can help individuals relearn how to voluntarily contract the target muscle and improve patient outcomes[17]. NMES has been used most extensively on the quadriceps muscle, with evidence that it improves quadricep cross-sectional area following atrophy, with and without voluntary contraction[18]. However, research into its effect on lumbar multifidus morphology, as assessed with MRI or ultrasound, is very limited. Coghlan et al. (2011) reported that a 6-week NMES intervention improved resting, but not contracting, multifidus thickness in CLBP patients.[19] A recent study investigating the effect of a 4-week Russian current intervention in young women with CLBP found a non-statistically significant increase in lumbar multifidus thickness, with medium effect sizes.[20] The results from NMES interventions on CLBP patient outcomes more broadly are also mixed. Hicks et al. (2016) trial found that combined trunk muscle training with NMES was more effective than a passive control intervention (heat + ultrasound + massage) at improving performance-based and self-rated function in older adults with CLBP.[21] Another study investigated the effect of a 4-week NMES protocol on CLBP patients saw no improvement in disability compared with matched controls[22], while Alrwaily et al. (2019) reported no additional benefit of NMES on self-reported pain and disability, fear-avoidance beliefs, and paraspinal muscle strength following a stabilization exercise program and combined stabilization + NMES program in patients with CLBP patients.[23]

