### Randomization

Participants will be randomized to treatment groups (1:1) using consecutively numbered sealed opaque envelopes (e.g., computer-generated randomization sequences) created by an individual not involved in the study.

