### Statistical analysis

We will perform an exploratory data analysis on participants’ sociodemographic characteristics and to verify normality assumptions. Paired t-tests or Wilcoxon sign-rank tests will be used assess within-group changes, pre-to-post intervention, for all primary outcome measures. Independent t-tests or Mann Whitney-U tests will be used to assess between-group changes, pre-to-post intervention, for all primary outcome measures. We will use either a two-way repeated measures ANOVA or Kruskall-Wallis tests to determine changes over time for secondary outcome measures. For all tests, statistical significance will be set at *p* < 0.05.

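### The 12 per group at 80% power is a within-arm paired figure; for the phasic-versus-combined comparison the same effect size gives about 56% power (66% if all 15 per arm complete)

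*Protocol article*

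**What the plan says.** The Sample size calculation section bases its effect size on two earlier reports of NMES, one of a 6-week course and one of a single session: "previous reports showed significant improvements in multifidus thickness at rest and during contraction with medium to large effect sizes". It continues: "we used a mean effect size of 0.9 to calculate our sample size at a level of confidence of 0.05 and 80% power". The result is "Accordingly, a sample size of 12 participants in each group was needed", and then "We increased the sample size to 15 participants in each group to account for potential drop-out". The section does not name the test, say whether it is one- or two-sided, or say which standard deviation scales the 0.9.

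The trial allocates participants 1:1 to two active settings of the same device (Study design; Randomization). The Background paragraph of the abstract says that "the primary aim of this study is to compare the effects of two muscle therapy protocols". The Statistical analysis section lists paired tests within groups and also states: "Independent t-tests or Mann Whitney-U tests will be used to assess between-group changes, pre-to-post intervention, for all primary outcome measures".

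The main-text Background also describes a 4-week Russian-current study in women with chronic low back pain, which "found a non-statistically significant increase in lumbar multifidus thickness, with medium effect sizes".

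**The concern.** A reader who meets 12 in each group at 80% power in a two-arm randomised trial will take the 80% to refer to the comparison between the arms. On the stated inputs it does not: 12 is what a single arm needs to detect its own change from baseline.

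The effect size has the same origin. The section describes it as improvement after NMES, which is not a difference between two NMES settings. Here both arms receive active stimulation at 3 kHz and differ in modulation (50 Hz, against 4 Hz and 50 Hz). A between-arm difference as large as a whole treatment improvement is therefore an optimistic assumption, and power computed at 0.9 is probably generous.

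What is at stake is how the result is read. If the phasic-versus-combined tests are non-significant and the article claims 80% power, readers may conclude that the two protocols work equally well. The data could not support that.

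**Working it through.** **Inputs.** From Sample size calculation: d = 0.9, α = 0.05, power 80%, 12 per group raised to 15. From Randomization: 1:1 allocation. Assumptions, because the article does not say: two-sided tests, and for the between-arm test, d is the difference in mean change divided by the SD of change.

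**Step 1: reproduce the stated 12.** For a paired t-test, power comes from the noncentral t distribution with n − 1 degrees of freedom and noncentrality d√n.
- n = 11: noncentrality 0.9 × √11 = 2.98, critical value 2.228, power 76.7%.
- n = 12: noncentrality 0.9 × √12 = 3.12, critical value 2.201, power 81.0%.

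The exact solution is n = 11.75, so 12. This matches the stated figure. The rise to 15 corresponds to an implied drop-out of 20%: 12 / 0.80 = 15.

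**Step 2: the same inputs between arms.** For an independent t-test with n per arm, the degrees of freedom are 2n − 2 and the noncentrality is d√(n/2).

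| n per arm | Noncentrality | Critical value | Power at d = 0.9 |
|---|---|---|---|
| 12 | 0.9 × √6 = 2.20 | 2.074 | 55.9% |
| 15 | 0.9 × √7.5 = 2.46 | 2.048 | 66.3% |
| 20 | 0.9 × √10 = 2.85 | 2.024 | 79.2% |
| 21 | 0.9 × √10.5 = 2.92 | 2.021 | 81.2% |

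The exact solution is n = 20.4, so 21 per arm. With the implied 20% drop-out that is 21 / 0.80 = 26.25, so 27 per arm or 54 in all. A one-sided test does not rescue the figure: it needs 16 per arm, and power is 68.8% at 12 and 77.6% at 15.

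**Step 3: what the planned numbers can detect between arms.** Solving for d at 80% power, two-sided:
- 12 per arm: 1.20 SD.
- 15 per arm: 1.06 SD.

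**Step 4: a smaller effect.** At 0.5 SD, an assumed medium effect:
- between arms, power is 22% (12 per arm) and 26% (15 per arm);
- within one arm, power is 35% (n = 12) and 44% (n = 15).

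**Step 5: precision.** The half-width of the 95% confidence interval for the between-arm difference, in SD units, is t × √(2/n).
- 12 per arm: 2.074 × √(2/12) = 0.85.
- 15 per arm: 2.048 × √(2/15) = 0.75.

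With an observed difference of zero, the interval would still include differences of about three quarters of an SD or more in either direction.

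**The case against.** The strongest reply is that the calculation is right for the analysis the authors had in mind. The Methods paragraph of the abstract names only paired t-tests for the primary outcomes, the aim at the end of the main-text Background speaks of the effects of the intervention without comparing arms, and the sample size section never says that the 80% applies between arms. This stands as far as it goes: 12 is a correct number for a paired test, and the fault is in what the number is taken to cover. It does not withdraw the comparative aim in the abstract or the between-group tests on all primary outcomes, and nothing in the article calls those tests exploratory or underpowered.

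A second reply concerns scale. If 0.9 were in units of the raw-score SD, the SD of change would be √(2(1 − r)) raw SDs, where r is the pre-post correlation. A between-arm test of change would then need 21, 17, 13 or 9 per arm at r = 0.5, 0.6, 0.7 or 0.8. So 12 per arm could suffice if r were slightly above 0.7. The article states neither this scale nor a correlation, so this is not its calculation, but it does make the 56% and 66% conditional on the SD-of-change reading.

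Third, 15 per arm are randomised, so 56% applies only if the whole drop-out allowance is used. That is fair, but full completion gives 66%, still short of 80%.

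Fourth, no equivalence conclusion is planned, and the studies behind the 0.9 are not at hand. Both points are true. The misreading is a risk, not a stated intention, and the doubt about 0.9 as a between-arm effect rests on how the article itself describes its source.

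**Conclusion.** The concern holds. On the stated inputs, 12 per group is the answer for a two-sided paired test within one arm. No independent-samples test on those inputs, one- or two-sided, gives 12 per arm at 80% power.

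For the comparison that the abstract names as the primary aim, power is 56% to 66% at d = 0.9, depending on drop-out, and 80% power exists only for differences of 1.20 to 1.06 SD. These figures assume a two-sided test and a standardised difference in change scaled by the SD of change. The 0.9 is probably generous for two active settings of one device, in which case true power is lower.

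**What to change.** Keep 30 participants and rewrite the sample size paragraph so that each power figure is tied to its comparison. Suggested text:

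> Twelve completers per arm give 80% power (two-sided 5% level) to detect a within-arm standardised change of 0.9. For the between-arm difference in change, 12 (15) completers per arm give 80% power only for a difference of 1.20 (1.06) SD of change, and 56% (66%) power for a difference of 0.9 SD. The between-arm result will be reported as an estimate with a 95% confidence interval, and a non-significant difference will not be interpreted as equivalence of the two protocols.

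The aim in the abstract and the Statistical analysis section should then make the same distinction, so that the reader knows which comparison the trial was sized for.

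The cost is a rewording, with no extra participants and no change to the tests. The drawback is that the stated power for the randomised comparison becomes visibly less favourable. Restoring 80% power between arms at 0.9 would instead take 21 completers per arm, about 54 randomised at the implied 20% drop-out.
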